**Original protocol**

**Title**: [Efficacy of Chinese Eye Exercises on Reduding Accommodative Lag in School-aged](http://clinicaltrials.gov/ct2/show/NCT01756287?term=chinese+ocular+exercise&rank=1) Children: a Randomized Controlled Trial

**Sponsor**: Beijing Tongren Eye Center, Beijing Tongren Hospital, Capital Medical

University, Beijing, China.

As for a randomized controlled trial on Chinese ocular exercises, only one department is not enough to perform it well. Our group finally included other departments, public school and evidence-based medicine center for study design and statistical analysis (School of public health, Capital Medical University, Beijing, China; Chinese Evidence-based Medicine Center, West China Hospital, Sichuan University, China ), a local hospital to organize the field work (Anyang Eye Hospital, Henan Province, China), and a foreign partner (School of Optometry and Vision Sciences, Cardiff University, Cardiff, UK) to ensure that our study can be well understood by western readers.

**ClinicalTrials.gov Identifier**: NCT01756287

**Study start date**: August 2012

**Estimated study completion date**: November 2013

**Background**:

Myopia is a public health problem worldwide, especially in some Asian countries like China, Singapore, and Japan.[^1^](#_ENREF_1) Chinese eye exercise, originating in 1963 with the theory of Traditional Chinese Medicine (Figure 1-4), is a kind of massage on acupuncture points around the eye to prevent myopia and alleviate visual fatigue.[^2^](#_ENREF_2) The exercise has been spreaded as a community ritual and living habit of primary and high school students for half a century in China. However, the prevalence of myopia in Chinese children increased remarkably in recent years.[^3-5^](#_ENREF_3) Therefore, the efficacy of Chinese eye exercise on preventing myopia or alleviating visual fatigue is widely questioned. Evidence from clinical trials of high level is needed to clarify that whether Chinese eye exercise is effective in slowing and preventing myopia progression, or at least in part in easing the symptoms related to myopia and visual fatigue.[^6^](#_ENREF_6)

[figure not shown]

Figure 1. Section 1 of Chinese eye exercises, massage on BL2 (cuanzhu)

[figure not shown]

Figure 2. Section 2 of Chinese eye exercises, massage on BL1 (jingming)

[figure not shown]

Figure 3. Section 2 of Chinese eye exercises, massage on ST2 (sibai)

[figure not shown]

Figure 4. Section 2 of Chinese eye exercises, massage on EX-HN5 (taiyang)

**Purpose**: To assess whether Chinese eye exercise is effective in altering accommodative lag, distant and near visual acuity, and visual symptoms in school-aged children in the short-term.

**Study type**: Interventional

**Study design**: Treatment, Parallel Assignment, Double Blind (Subject, Investigator, Outcomes Assessor), Randomized, Efficacy Study

**Estimated enrollment**: 180

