**Arms and Assigned Interventions:**

1. **Experimental**: **Standardized Chinese eye exercise**. The participants are trained with standardized Chinese eye exercise which contains accurate position of acupuncture points and appropriate pressure on the points.
2. **Sham comparator: Nonstandardized eye exercise.** The participants are trained with nonstandardized eye exercise performed on wrong positions where no acupuncture points at all.
3. **No intervention:** **Eye closure**. The participants are told to close eyes and don’t do eye exercise at all.

The locations of acupoints of standard Chinese eye exercises (SCEE) and sham point eye exercises (SPEE) are shown in **Appendix 1**.

To guarantee the performance quality of eye exercises, one independent investigator will first demonstrate the procedures of eye exercises and explain the principles for each child. Children will be asked to practice respective exercises under the instruction of the independent investigator for at least three times. During this period, mistakes will be repeatedly corrected until the children perform the eye exercises accurately. Finally, all participants’ performance quality of exercises will be assessed and scored by two independent judges. The assessment covered location, force, scope and frequency of the massage (**See Appendix 2**). Scores greater than 30/40 and differences between two judges less than 5 points were defined as qualified.

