**Outcome measures**:

**Primary outcome measures**: accommodative lag before and after the intervention immediately

**Secondary outcome measures**: distant and near visual acuity before and after the intervention immediately

**Other Pre-specified outcome measures**: Self evaluation of visual discomfort score before and after the intervention (**Appendix 3**)

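### The unqualified double-blind label does not fit the eye-closure arm, the trainer or the performance judges, and the self-rated discomfort score is open-label in any comparison with eye closure

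*Protocol*

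**What the plan says.** The Study design line, which follows the Background, gives the masking as "Double Blind (Subject, Investigator, Outcomes Assessor". It applies to the trial as a whole, and no later section narrows it.

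Arms and Assigned Interventions sets out three arms: the standardized exercise, a sham described as "nonstandardized eye exercise performed on wrong positions where no acupuncture points at all", and a no-intervention arm in which "The participants are told to close eyes and don’t do eye exercise at all". The same section describes the training, in which "one independent investigator will first demonstrate the procedures of eye exercises and explain the principles for each child" and mistakes are then corrected until the child performs accurately. After that, "performance quality of exercises will be assessed and scored by two independent judges", and location is one of the things scored.

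Outcome measures lists accommodative lag as primary and distance and near acuity as secondary. As another pre-specified outcome it lists "Self evaluation of visual discomfort score before and after the intervention". Appendix 3 shows that instrument: ten items, each marked by the child from 0 to 10. Visual symptoms are also named in the Purpose.

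**The concern.** The design line claims masking for three roles across three arms, while the arm descriptions and training procedure take it away from some of those roles. This is a conflict within the Protocol, not a detail that a separate analysis plan could supply.

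What is at stake is how the discomfort result can be read. When the child does the rating, the child is the outcome assessor. A child who knows that no exercise was done may report differently from one who has just been taught and corrected through an exercise, whatever the exercise does to the eyes. A reader who relies on the design line would take a difference from eye closure as double-blind evidence of symptom relief, when expectation could account for some or all of it.

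**Working it through.** No masking figure is stated, so there is nothing to reproduce. The check sets the declaration against the arms and procedures, role by role and comparison by comparison.

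**Inputs**
- Declared masking: subject, investigator and outcomes assessor, unrestricted (Study design).
- Three arms: standard, sham, eye closure (Arms and Assigned Interventions).
- Ages 10 to 16 (Eligibility of the participants).
- Estimated enrolment 180 (under Background). The allocation ratio is not given.
- Discomfort rated by the child (Outcome measures; Appendix 3).

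**By role**
1. *Subject, eye closure.* A child of 10 to 16 who is told to close the eyes and not to exercise cannot mistake this for either exercise arm. Subject masking fails here with certainty.
2. *Subject, standard or sham.* Both groups massage points around the eye under instruction, so a child could in principle not know which version was taught. Against this, the Background calls the exercise "a community ritual and living habit of primary and high school students for half a century in China", and the trial enrols children of school age. Some may recognise that the sham points are not the usual ones. Masking is possible but uncertain.
3. *Investigator who trains.* Demonstrating the movements and correcting errors requires knowledge of the assigned exercise. This role cannot be masked.
4. *Performance judges.* They watch the exercise and score where it is done. Appendix 2 names the standard anatomical sites. They are exposed to the assignment and cannot be counted as masked.
5. *Examiner for lag and acuity.* Nothing in the Protocol obliges this person to see the exercise. Masking is feasible in all three arms if the roles are kept apart.
6. *Assessor for discomfort.* The assessor is the child, so masking is whatever items 1 and 2 allow.

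**By comparison, discomfort score**

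Three arms give 3 × 2 / 2 = 3 possible pairs.

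| Pair | Is the child masked? |
| --- | --- |
| Standard vs sham | Possible, uncertain |
| Standard vs eye closure | No |
| Sham vs eye closure | No |

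Two of the three pairs are therefore open-label for this outcome. The Protocol does not say which pairs will be tested, so this counts possible comparisons, not planned ones. If allocation were equal, which is an assumption, the arm that is certainly unmasked would hold 180 / 3 = 60 children.

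**The case against.** The best defence is that the label is registry-style shorthand and the design behind it is sound. A sham on non-acupoints is a recognised way to mask subjects between two active-looking arms. The trainer and judges are called independent, which suggests that they are separate from those who examine the eyes. The primary outcome is not a self-rated scale. The discomfort score ranks below the primary and secondary outcomes, and no sample size or error rate depends on the label.

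Most of this stands, and it limits the point. A reader might go further in four ways that the Protocol does not support.

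- *That subject blinding fails throughout.* Between standard and sham it is only in doubt. How far the sham points lie from the real ones is in the Appendix 1 figure, which is not available here, and what children are told about the arms is not known either. The Background speaks of a living habit and gives no frequency.
- *That all investigators are unmasked.* The training procedure shows this for the trainer and exposes the judges. Others could remain masked.
- *That expectation biases accommodative lag.* The Protocol does not say how lag is measured or that it depends on the child's effort, so this cannot be shown.
- *That the sponsor will report the discomfort score as blinded.* The Protocol does not say so. The risk is that the design line invites that reading.

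What the defence does not answer is the eye-closure arm. No division of roles hides from a child that no exercise was done, and the design line makes no exception for it.

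**Conclusion.** The masking statement is wrong as written. It is false for subjects in one of three arms and for the trainer, and it cannot be sustained for the performance judges. For subjects it can hold only between standard and sham, and uncertainly. For the examiner of lag and acuity it can hold throughout.

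The certain consequence is that the discomfort score is open-label in any comparison with eye closure. This follows from the Protocol's own text and needs no outside figure. The doubt about standard versus sham rests on the assumption that enrolled children know the usual points well enough to notice a change.

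The severity is moderate. Visual symptoms are part of the stated Purpose, so the correction changes what the trial may conclude about them. The outcome certainly affected is an other pre-specified one, however, and the case against the primary outcome is not made.

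**What to change.** Replace the single label with a statement by role and by comparison:

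- the examiner of accommodative lag and acuity is masked to arm;
- subjects are masked at most between standard and sham exercise;
- eye closure is open;
- the trainer and the performance judges are unmasked and take no outcome measurements.

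For the discomfort score, base any claim described as blinded on standard versus sham only, and label its comparison with eye closure as unblinded. That comparison can still be tested and reported; it need not be reduced to description.

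The cost is a few lines in the design statement and in the text on the discomfort score. No arm, sample size or primary analysis changes. Barring the trainer and judges from measurement may only make explicit what the word independent already implies. The downside is a less favourable blinding statement.

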**Eligibility of the participants**

Ages eligible for study: 10 years to 16 years

Genders eligible for study: both

**Inclusion criteria**:

- - 1. Visual acuity: 20/20 or better in each eye;
    2. Spherical error ranging from +0.5 D to -6.0 D and astigmatism less than 1.5 D in each eye, anisometropia less than 1.0 D between the two eyes
    3. No strabismus, amblyopia and any other ocular or systematic diseases that may affect the refractive development

**Inclusion criteria**:

1. Currently using other interventions to control myopia progression (acupuncture, massage, drugs ear needles and so on)
2. Unable to cooperate with the ocular examination and questionnaire survey

**Arms and Assigned Interventions:**

1. **Experimental**: **Standardized Chinese eye exercise**. The participants are trained with standardized Chinese eye exercise which contains accurate position of acupuncture points and appropriate pressure on the points.
2. **Sham comparator: Nonstandardized eye exercise.** The participants are trained with nonstandardized eye exercise performed on wrong positions where no acupuncture points at all.
3. **No intervention:** **Eye closure**. The participants are told to close eyes and don’t do eye exercise at all.

The locations of acupoints of standard Chinese eye exercises (SCEE) and sham point eye exercises (SPEE) are shown in **Appendix 1**.

To guarantee the performance quality of eye exercises, one independent investigator will first demonstrate the procedures of eye exercises and explain the principles for each child. Children will be asked to practice respective exercises under the instruction of the independent investigator for at least three times. During this period, mistakes will be repeatedly corrected until the children perform the eye exercises accurately. Finally, all participants’ performance quality of exercises will be assessed and scored by two independent judges. The assessment covered location, force, scope and frequency of the massage (**See Appendix 2**). Scores greater than 30/40 and differences between two judges less than 5 points were defined as qualified.

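### Subjects are declared blind, but children familiar with the real exercise could recognise a wrong-position sham, leaving the standard-versus-sham comparison of self-rated discomfort open to expectation

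*Protocol*

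**What the plan says.** The Study design line of the Protocol lists the masked parties as "Double Blind (Subject, Investigator, Outcomes Assessor", so the children count as blind to their arm.

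The Background describes the real exercise as a "community ritual and living habit of primary and high school students for half a century in China". The eligibility section states "Ages eligible for study: 10 years to 16 years", so the sample comes from that same population.

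Under Arms and Assigned Interventions, the sham children are "trained with nonstandardized eye exercise performed on wrong positions where no acupuncture points at all". The training paragraph there has an independent investigator "demonstrate the procedures of eye exercises and explain the principles for each child", followed by at least three practices with correction until performance is accurate. This training is described once, with no distinction between the two exercise arms. The real and sham locations are given in Appendix 1, a figure that is not available in the text reviewed.

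Under Outcome measures, the primary outcome is "accommodative lag before and after the intervention immediately". The third tier is "Self evaluation of visual discomfort score before and after the intervention"; Appendix 3 shows that the child rates ten items from 0 to 10. Visual symptoms are also named in the Purpose.

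The eligibility item nearest to prior exposure reads "Currently using other interventions to control myopia progression" (in the second list headed Inclusion criteria). It concerns other treatments and does not require children to be new to the eye exercise.

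**The concern.** A sham protects a self-reported outcome only as far as the participant cannot tell it from the real treatment. Here the sham differs from the real exercise in where the fingers are placed, and the protocol's own Background suggests that many eligible children already know the routine. The instruction to explain the principles does not say what may be disclosed. Nothing in it stops a child from learning whether the points being taught are acupoints.

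Standard versus sham is the contrast that separates an acupoint effect from the effect of massage around the eye in general. If some sham children recognise their arm and rate their discomfort differently for that reason, the difference between arms mixes expectation with any acupoint effect. The planned data hold nothing that would show how far this happened. A larger sample would not help, because the bias does not shrink with sample size. What is at stake is the conclusion on visual symptoms.

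**Working it through.** The protocol gives no figure for sham credibility, recognition or expectation, so there is nothing to reproduce. The check has two parts.

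**1. The statements set side by side**

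- Subjects are declared blind (Study design).
- The real exercise is habitual among schoolchildren (Background), and schoolchildren aged 10 to 16 are enrolled (Eligibility).
- The sham is defined by its wrong positions, and the principles are explained to each child (Arms and Assigned Interventions).
- Discomfort is rated by the child before and after the session (Outcome measures, Appendix 3).

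Together these show that recognition is possible and that one outcome is exposed to it. They do not show how many children would recognise the sham, or which way their ratings would move.

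**2. An illustration of size**

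Inputs:
- Enrolment of 180 (Protocol, Estimated enrollment).
- Three arms with no ratio stated; equal allocation is assumed, so n = 180 / 3 = 60 per arm.
- Significance level 0.05 (Statistical analysis); two-sided is assumed.
- No true effect of treatment (assumption).
- A share p of sham children recognise the sham, and each shifts the rating by e SD (both assumed).

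Mean shift between arms: d = p × e.

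Two-sample t test with 118 degrees of freedom, no covariate and no multiplicity adjustment. Noncentrality = d × √(n/2) = d × √30 = d × 5.477. The false-positive rate is the probability that |t| exceeds the critical value 1.980.

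| p | e (SD) | d = p × e (SD) | Noncentrality | Significant with no true effect |
|---|---|---|---|---|
| 0.25 | 0.2 | 0.05 | 0.274 | 5.8% |
| 0.5 | 0.3 | 0.15 | 0.822 | 12.9% |
| 1 | 0.3 | 0.30 | 1.643 | 37.1% |
| 1 | 0.5 | 0.50 | 2.739 | 77.5% |

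A normal approximation gives nearly the same: 37.6% at 0.30 SD and 78.2% at 0.50 SD. At p = 0.5 and e = 0.5 (d = 0.25 SD) it gives about 28%.

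The rates are symmetric in the sign of d, so they hold whether expectation favours the standard arm or the sham. They also show that recognition by half the sham children is not harmless: the rate is 12.9% with e = 0.3 and about 28% with e = 0.5. A rule that allowed an acupoint claim unless most sham children recognised the sham would therefore not protect the conclusion.

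**The case against.** The strongest reply is that recognition is unproven. The Appendix 1 locations cannot be seen, and sham points close to the real ones would be harder to spot. This stands, and it limits the point to what could happen.

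A reader might infer that only sham children are moved away from what they usually do. The document does not support that. Both exercise arms get the same demonstration, practice and correction, and the standard arm is itself trained in accurate position and pressure. Children in that arm may also be moved off their habit, since the Background does not say how accurately children usually find the points.

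A reader might also infer that the bias would favour the standard exercise. The Background itself says that the efficacy of the exercise is widely questioned, and an unfamiliar exercise could raise expectation as well as lower it. The text fixes no direction.

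Nor does the point by itself undermine the primary comparison. Accommodative lag should be less exposed to expectation than a self-rating, though this is a judgement: the protocol does not name the method of measuring lag. The affected outcome is in the third tier.

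The percentages are illustrative and come from an unadjusted t test, whereas the protocol plans ANCOVA or a nonparametric test. This stands too.

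Finally, one could call this a missing blinding check that belongs in an analysis plan. That does not hold. What the children are told and asked on the day is fixed by the protocol and cannot be recovered at analysis.

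**Conclusion.** The point holds in a limited form. Subject blinding is declared, yet the protocol's own description of the exercise as habitual, its wrong-position sham and its unrestricted explanation of principles mean that some sham children could recognise their arm. Expectation could then bias standard versus sham on self-rated discomfort, in a direction and by an amount that cannot be determined from the protocol.

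The range of about 6% to 78% false positives is conditional on assumed recognition shares of 0.25 to 1, assumed shifts of 0.2 to 0.5 SD and an assumed 60 children per arm. At the low end the inflation is negligible. The protocol as written gives no way of learning which end applies. It would be too strong to say that blinding fails, that the standard arm is favoured or that the primary result is compromised. The point is worth acting on because the correction is cheap and the Purpose includes visual symptoms.

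**What to change.** 1. **Arms and Assigned Interventions.** Replace the instruction to explain the principles with one identical neutral script for both exercise arms, which does not say which points are acupoints.
2. **Outcome measures / post-session form.** After the last outcome measurement, ask children in both exercise arms whether the places they massaged were the usual ones for eye exercises (yes / no / don't know). Report the answers by arm.
3. **Statistical analysis.** State that any standard-versus-sham difference in discomfort will be reported as open to expectation, alongside the recognition figures, and will not on its own be called an acupoint effect. Set no threshold of recognition below which the claim becomes allowed. State that the acupoint conclusion rests primarily on accommodative lag.

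The cost is one extra question per child in the exercise arms, a short script and a few sentences in the protocol, with no added staff, visits or participants. The downside is a more cautious symptom claim. The question measures recognition and does not prevent it; only the script can reduce it, and only in part.

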**Outcome measures**:

**Primary outcome measures**: accommodative lag before and after the intervention immediately

**Secondary outcome measures**: distant and near visual acuity before and after the intervention immediately

**Other Pre-specified outcome measures**: Self evaluation of visual discomfort score before and after the intervention (**Appendix 3**)

